## Discussion

Neonatal jaundice is a common condition that affects a significant proportion of newborns, with a prevalence ranging from 2.4% to 15% (25). Probiotic supplementation has been shown to improve neonatal jaundice recovery and reduce phototherapy's side effects by regulating bacterial colonies and enhancing immunity (26–28). Previous studies have evaluated the clinical value of probiotic supplementation in treating neonatal jaundice and have provided evidence that combining conventional treatment with probiotic supplementation, including Bifidobacterium, Streptococcus brachii, Chlamydia butyrate, probiotic oligosaccharide, and Bacillus subtilis, significantly improves the therapeutic efficacy of neonatal jaundice (16, 29–32). In addition, probiotic supplementation has been shown to significantly improve neonatal jaundice by reducing total bilirubin levels and accelerating jaundice regression, which can also lead to a reduction in the duration of phototherapy and hospitalization (33–35).

The following limitations of this trial should be considered. First, this study will not include a pure blank control group without phototherapy, and the control group with phototherapy alone will lack data from healthy newborns in the same region and period as a reference. Second, the trial is single-blinded, and the investigators would be aware of the trial-group assignments, which might influence the results. Third, the sample size would be relatively small, the trial will focus on a short observation period with no long-term follow-up of patients, and the study will be conducted only in a single center. Therefore, the methodological quality of clinical trials of probiotic supplementation for neonatal jaundice would need further improvement, and well-designed, larger randomized double-blind trials are necessary to further confirm the efficacy of probiotics.

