**Methods and analysis:**

A total of 100 jaundiced newborns aged two weeks or younger will be included in this randomized, single-blind (the parents knew, but the neonatologists did not know), single-center controlled trial to receive either 10^9^ colony-forming units of AB-GG, Bb-12, M-16V, a combination of the three probiotics with blue-light phototherapy, or blue-light phototherapy alone. The experimental group will be treated with oral probiotics once daily for 30 days, while the control group will receive only blue-light phototherapy. The follow-up duration will last 30 days. The primary outcomes include changes in gut microbiota, metabolomics, and the incidence of phototherapy side effects, assessed after each phototherapy session, as well as on days 10, 20, and 30.

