### Experiment and subject setup

The trial will be conducted by enrolling newborns admitted to the NICU unit of East Hospital of Shanghai Sixth People's Hospital. As a tertiary hospital, it discharges over 300 newborns annually, including approximately 100 preterm infants and about 150 jaundiced newborns, ensuring a sufficient source of potential participants. All researchers involved have obtained GCP certifications and are either members of the current clinical pediatric team or the pediatric graduate team, guaranteeing the smooth development and execution of basic and clinical trials at any time. The East Hospital of Shanghai Sixth People's Hospital has established a clinical research center and obtained clinical trial qualifications. Recruitment started in June 2021 and will be completed over the following there years.

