The investigator will re-check the inclusion/exclusion criteria on the first day, perform patient management, conduct detailed physical and serologic examinations prior to phototherapy, and record the adverse events described in Table 1. They will collect stool and blood samples from the subjects. Subjects will receive the first 12 h of phototherapy and the assigned probiotics before phototherapy. After 12 h of phototherapy, researchers will observe phototherapy-related side effects (including body temperature, rash, stool frequency and shape, etc.), record information, collect stool samples, and measure TCB. On the next day, after 6–8 h of rest, the infant will receive a second 12 h phototherapy session while the assigned probiotics are orally administered, and the researchers will again assess and collect fecal samples. The same process will be followed for the third day, and if necessary, subjects may continue with the fourth and fifth 12 h phototherapy sessions, with at least 6 h of rest after each phototherapy session. Stool collection will still be required after each phototherapy session. Subjects will not require further phototherapy and will be discharged once they meet the discharge criteria.

Upon meeting the discharge criteria, the investigator will perform subject management, a detailed physical examination, serological testing, and evaluation of adverse events prior to discharge. Study follow-up on days 10, 20, and 30 will be completed at the outpatient follow-up for hyperbilirubinemia, during which stool and related data will be collected. Infants in the experimental group will continue to receive their assigned oral probiotics during hospitalization after enrollment and during outpatient follow-up for one month.

Stool samples weighing 500 mg and blood samples measuring 0.5 microliters were collected from each subject. The stool samples will be stored at −80°C after freezing, while the blood samples will be tested immediately. There would be no restrictions on the feeding patterns of both the experimental and control groups during the study. Parents are allowed to freely choose between breastfeeding, artificial feeding, and mixed feeding.

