### Randomization

(1)The randomized scheme of this experiment will be as follows: 100 cases are planned to be enrolled and divided into 5 groups: C0 (pure phototherapy group), T1 (treatment group 1), T2 (treatment group 2), T3 (treatment group 3) and T4 (treatment group 4), with 20 cases in each group.(2)The random system parameters will be set as follows:
•Random system: Taimei Medical eBalance random system•Random method: block random•Block length: 5•Number of blocks: 20•Random number: P001–P100.

The random operation steps would be as follows: The random-related parameters are determined according to the project's random scheme. The eBalance stochastic system is configured according to random parameters. The eBalance random system generated a random grouping table according to the configuration (calling SAS software). The eBalance random system exported the random grouping table.

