### Blinding

The trial is designed to be single-blind. All neonatologists wouldn't be aware of the group assignments throughout the study, while the parents would be aware of their group assignment to the experimental or control groups.

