### Allocation concealment

Based on the randomization table, each enrolled subject will be assigned a serial number in order, which will correspond to one of the following groups: C0 (phototherapy only), T1 (M-16V combined with phototherapy), T2 (Bb-12 combined with phototherapy), T3 (AB-GG combined with phototherapy), and T4 (M-16V combined with Bb-12 combined with AB-GG combined with phototherapy).

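### The blinding statements conflict, so blind scoring of the judged side effects is not established; if investigators do know the groups, fixed blocks of five also expose enrolment

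*Protocol article*

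**What the plan says.** All references are to the protocol article.

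- **Abstract, Methods and analysis:** the trial is "single-blind (the parents knew, but the neonatologists did not know".
- **Blinding:** "All neonatologists wouldn't be aware of the group assignments throughout the study". Families, by contrast, are told whether their infant is on probiotics or is a control.
- **Discussion, limitations:** "the trial is single-blinded, and the investigators would be aware of the trial-group assignments, which might influence the results".
- **Experiment and subject setup:** the researchers "are either members of the current clinical pediatric team or the pediatric graduate team".
- **Study procedure:** participating pediatricians obtain consent. After each phototherapy session, "researchers will observe phototherapy-related side effects (including body temperature, rash, stool frequency and shape, etc".
- **Endpoints:** the primary endpoint is the incidence of clinical side effects. The list is open-ended and includes rash and feeding intolerance as well as diarrhea, fever, vomiting and convulsions.
- **Interventions, adverse events text:** one group, read here as the control group, has nothing added to its milk. No placebo is described.
- **Randomization:** five groups of 20, with "Block length: 5", 20 blocks and numbers P001 to P100. The table is generated in and exported from the eBalance system.
- **Allocation concealment:** "each enrolled subject will be assigned a serial number in order, which will correspond to one of the following groups".

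**The concern.** Two parts of the article give the doctors as blind, and a third gives the investigators as aware. The article never separates these roles. The Discussion sentence also does not say who the blinded party would then be, since the Blinding section has already said that parents know.

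Two things are at stake. First, rash, feeding intolerance and an open-ended residual category need judgement, so an assessor who knows the group can score them differently between arms. Second, if the people who enrol also know past assignments, a block exactly as long as the number of arms lets them work out some future ones. They could then influence which infant is entered, and when.

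**Working it through.** **Step 1. The roles side by side.**

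- Enrolment: participating pediatricians (Study procedure).
- Scoring of side effects: researchers (Study procedure).
- Who the researchers are: clinical pediatric team or pediatric graduate team (Experiment and subject setup).
- Blind: all neonatologists (Abstract; Blinding).
- Not blind: investigators (Discussion) and parents (Abstract; Blinding).

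No section names an assessor who stands outside these teams, and none says on which side of the line the side-effect assessor falls. The article supports neither a firm statement that the assessor is blind nor a firm statement that the assessor is not.

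**Step 2. The plan's own block figures.** 20 blocks × 5 = 100 infants, which matches P001 to P100. With five equal arms, each block of 5 holds each arm once, and 20 blocks × 1 = 20 per arm, as planned. The scheme is arithmetically sound.

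**Step 3. Probiotic or control known in advance.** Assume that a person knows the block length and whether each earlier infant in the block was probiotic or control. Let the single control fall at position k, equally likely to be 1 to 5. Once the control has appeared, everyone left in the block must be probiotic. If the first four were all probiotic, the fifth must be control. The number of infants whose status is certain beforehand is:

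- k = 1: 4
- k = 2: 3
- k = 3: 2
- k = 4: 1
- k = 5: 1

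Mean = (4 + 3 + 2 + 1 + 1)/5 = 11/5 = 2.2 per block. 2.2/5 = 44%, or 20 × 2.2 = 44 of 100 infants. In a single block the share runs from 1/5 (20%) to 4/5 (80%).

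**Step 4. Exact arm known in advance.** For someone who knows the exact arms of the first four infants, the fifth is fully determined: 1 of 5 (20%), or 20 of 100 infants.

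**Step 5. Best guess of the exact arm.** With the same knowledge, the expected number of correct guesses per block is 1/5 + 1/4 + 1/3 + 1/2 + 1 = 2.28. 2.28/5 = 45.7%, against 1/5 = 20% by chance.

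**Step 6. The condition.** Steps 3 to 5 need knowledge of both the earlier assignments and the block length. Under the Discussion's account, enrolling staff could have the first. Under the Blinding section's account, if it covers them, they do not, and a guess of the exact arm is right only at the chance rate of 20%.

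**The case against.** The strongest reply is that the statements do not strictly contradict each other. Neonatologists and investigators are different words, and researchers may come from the graduate team, so the treating neonatologists could be blind while other study staff are not. That is possible. But the article does not say so, and it does not say which of these people scores the primary endpoint. The gap therefore remains.

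A second reply is that investigator awareness is openly listed as a limitation, and that the article itself calls for larger double-blind trials. Disclosure is to the authors' credit, but here the disclosed limitation disagrees with the Methods, so a reader cannot tell which to believe.

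A third reply is that a short article may leave to the full protocol how numbers are released and who holds the table. This stands. The brevity of the Allocation concealment section is not counted against the plan. The block length is stated, however, and can be judged as it stands.

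Three stronger readings are tempting and go too far:

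- A reader might infer that nobody who scores the primary endpoint is blind. That follows only if the Discussion is right and covers the side-effect assessors.
- A reader might infer that upcoming assignments are simply predictable. That needs both conditions in Step 6, and no section says that ward staff hold the list or know the block length.
- A reader might infer that the results will favour the probiotics. The documents show a risk, not an effect, and give no figure for its size. Fever, vomiting and convulsions are easier to count than rash or feeding intolerance, and sequencing, metabolomics and serum bilirubin are less exposed.

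**Conclusion.** The concern holds as an unresolved inconsistency with a conditional consequence. Because the article does not establish blind scoring, the judged components of the primary endpoint are at risk of bias. The size of that bias cannot be computed from the document.

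The enrolment risk is secondary and depends on the Discussion being right. The average of 44% of infants known in advance as probiotic or control, and the 20% with a fully known arm, are upper figures. They assume complete knowledge of earlier assignments in the block and of the block length. If the Blinding section holds for those who enrol, the fixed block does little harm. The point should be corrected, but it does not by itself invalidate the design, and no sample size figure changes.

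**What to change.** 1. Reconcile the Abstract, the Blinding section and the Discussion by stating the blinding status of each role: the person who enrols, the person who gives the product, and the person who assesses side effects.
2. Have the side-effect form completed by existing staff who have no access to the randomization list and no part in preparing feeds. The article does not say whether the ward can arrange this. If it cannot, describe the trial as open-label.
3. For any allocations still to be made, use mixed block lengths of 5 and 10 that are not disclosed to the ward, released one at a time after consent. Post the change to the registry, as the Trial design section requires for significant modifications. Recruitment began in June 2021 and was planned over about three years, so few or no allocations may remain. Items 1 and 2 apply to the text in any case.

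The cost is a division of duties among existing staff, a small reconfiguration of the randomization system and a registry update. Assessment times and sample size stay as they are. Parents will still know the group and could reveal it to an assessor, so that limitation should stay in the Discussion.

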### Harms

The principal investigators will conduct a weekly review of all adverse events and conduct an investigator meeting when necessary to assess the risks and benefits of the study. The committee will monitor the safety and efficacy of the data to make recommendations for further research.

### Auditing

The hospital ethics committee requires the study to be reviewed every 12 months and may adjust the frequency of reviews based on the actual progress of the study.

## Data Availability

The datasets presented in this article are not readily available because of ongoing research. Requests to access the datasets should be directed to the corresponding authors.
